#### Aim 3: Pilot Trial

We will pilot test the chhaupadi intervention in one community and include a matched control community located sufficiently far away to minimize spillover effects. The trial will focus on assessing feasibility and acceptability, as well as collecting preliminary data on knowledge, attitudes, behaviors, and health outcomes expected to be impacted by the intervention. The intervention will be delivered by trained community organizers with expertise and experience conducting health interventions in rural Nepal. As a research organization, our partner Bikash Shrot Kendra will provide support with intervention evaluation and ensure implementation is consistent across pilot communities. We estimate that the intervention will include 8‐10 two-hour sessions in the community, over the course of 4 months, estimated based on other intervention approaches for shifting cultural norms.

Quantitative outcome measures will be used to assess feasibility and acceptability, and results will inform the design of a subsequent trial. We will conduct focus group discussions (FGDs) with participants and the intervention team to discuss challenges, barriers, and opportunities to adjust the intervention material and protocol (mid-point and post). Last, we will follow up with participants six months after completion to further assess outcomes.

### Analysis

#### Overview

We will use StataSE for quantitative analyses. For qualitative analyses, all audio-recorded data will be transcribed and translated from Nepali to English by trained translators who are fluent in both languages. Photographs, visuals, and diagrams collected as part of the HCD activities will also be transcribed/translated using standardized spreadsheets in Microsoft Excel. Qualitative analyses will be conducted in Dedoose. For all aims, we will collect demographic information about each study participant, which will be used to describe the study sample based on key demographic variables. Intervention reporting will follow the Template for Intervention Description and Replication (TIDieR) checklist (Checklist 1 provides more information).

#### Specific Analysis Plans for Aim 1

In the analysis of studies/intervention reports for the RS, we will scrutinize the evidence, specifically each study/intervention by context, mechanisms, and outcomes, aligned with RS standards [45]. Context will explore the conditions under which the intervention impacts outcomes (eg, geographic location and cultural norms). Mechanisms, or processes operating within an intervention, will explore how participants use the resources offered through the intervention. Outcomes will include the consequences of the study/intervention, intended or unintended, resulting from the interaction between context and mechanism (eg, improved mental health outcomes and reduced number of women practicing chhaupadi) [56]. We will use these components to describe the extent and circumstances under which an intervention works or does not, and to test and refine our theoretical framework drafted in Step 1. Screened data will be exported from Qualtrics forms and discussed with the review team to create data evidence tables [45] organized by key theme (eg, context, mechanism, and outcome). Next, we will assess the data for a chain of inference to explore connections across studies/interventions, as is standard practice in RS [45,56].

KIIs (conducted in Nepali or English based on participant preference) will be audio recorded, transcribed, and translated into English as necessary. Two coders will analyze data thematically in NVivo (Lumivero). Presentation of our findings will be organized according to the theoretical framework developed and refined throughout the RS, using constructs of context, mechanism, and outcome. Recommendations will be established via a final brainstorming session with experts from Step 1. Results will be reported according to the RAMESES for quality and publication [44].

#### Specific Analysis Plans for Aim 2

The resulting data from the HCD workshops will include the following. (1) Field notes: reflections on what worked effectively and what could be improved. (2) HCD artifacts: audio recordings and photographs of the outputs for all HCD activities (eg, stakeholder map, walk a mile immersion, photo journaling, experience diagram, impact ladder, etc) transcribed/translated into standardized Excel sheets for further analysis. This will include direct quotes from the activity discussion from audio recordings, which will be transcribed and translated into English. (3) FGDs and KIIs: audio recordings of FGDs and KIIs will be transcribed and translated from Nepali to English. All data will be qualitatively analyzed thematically in Dedoose and guided by the Health Stigma and Discrimination Framework [59].

Based on findings from the co-analysis workshops, the PI will lead the development of the intervention materials, implementation protocol, and training manual. The educational consultant will be responsible for creating presentations providing overviews of each intervention module, including material lists, goals, and activity instructions. Intervention materials will include written content (in English, Nepali, and local dialect, if necessary), illustrative graphics, an implementation guide, and activity instructions. The graphic design company will ensure that all intervention materials, such as training instructions or an implementation guide, are in accordance with the vision of the CDT members. Based on piloting, we posit that the core intervention could include (1) activities at multiple levels of the social ecological model, considering the influence of individual knowledge, family beliefs, social pressure, and policies on menstrual behaviors; (2) multiple target groups for behavior change, including but not limited to mothers/women, youth, female community health volunteers, and religious leaders, each with their own behavior change messaging and approaches (eg, community group sessions vs radio/newspaper vs one-on-one education); and (3) sessions over the course of several months, since social norms and behaviors require considerable time to shift.

We will elicit feedback on the intervention content and protocol using cognitive interviewing, an evidence-based method for determining if the proposed tool fulfills its planned purpose [60], with 10 experts from MHMPA and BSK before the pilot test in aim 3.

#### Specific Analysis Plans for Aim 3

This pilot is not intended to power between-arm comparisons; however, findings will allow for an initial assessment of feasibility and acceptability in preparation for a future randomized controlled trial. Aligned with pilot study best practices, we will describe the intervention sample using participant characteristics (n and % for categorical variables and mean and SD for continuous variables). We will calculate the approached-to-enroll and completion rates compared with prespecified benchmarks (Table 3) and report the percent of sessions completed as planned, participant completion rates, as well as outcomes for each measure (frequency and %, mean and SD, or median and range). Since this is an initial pilot test, no formal efficacy tests will be conducted by the comparison group; however, we will run exploratory analyses on outcomes by caste/ethnicity, age, education, and religion for descriptive purposes only. We will also test for differences in potential confounders between the intervention and control groups and adjust for them in regression models. All quantitative analyses will be conducted in Stata SE (StataCorp LLC).

**Table 3. T3:** Measures and tools for aim 3 data collection.

Measures/tools	Pre	Mid	Post	6 month
Demographics (eg, sex, caste/ethnicity, religion, education, occupation, and age)	✓			
Intervention Pilot Testing Measures				
Enrollment: Enrollment pace, and retention (Benchmark: ≥80% of approached individuals enrolled; ≥80% retention)			✓	
Acceptability: For participants and implementers, acceptability of intervention measure [61] a valid and reliable measure of acceptability with 4 items on a 5-point Likert (Benchmark: ≥3.5) and open-ended questions on acceptability of intervention components			✓	
Appropriateness: For participants, the intervention appropriateness measure [61] a valid and reliable measure of appropriateness with 4 items on a 5-point Likert scale (Benchmark: ≥3.5)			✓	
Feasibility: Extent to which the intervention is successfully executed. Feasibility of Intervention Measure [61] a valid and reliable measure of feasibility with 4 items on a 5-point Likert scale (Benchmark: ≥3.5)			✓	
Challenges, barriers, opportunities: FGDs^a^ with implementers (n=1) and participants (n=2)		✓	✓	
Exploratory intervention outcome measures				
Mental Health: Beck Anxiety Inventory Validated for Nepal [62] 21 items, 4-point Likert	✓		✓	✓
Reproductive Health Questionnaire [17]	✓		✓	✓
Chhaupadi knowledge, attitudes, and behaviors	✓		✓	✓
Self-efficacy: Generalized Self-Efficacy Scale, 10 items, 4-point Likert [63]	✓		✓	✓

a FGD: focus group discussion.

Qualitative analyses of open-ended and FGD data will be coded thematically in NVivo. We will professionally transcribe and translate the data, and 2 independent members of the research team will analyze data using template analysis to enhance rigor, allowing for inductive and deductive analysis [64].

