### Specific Aims

Three specific aims guide our inquiry:

Aim 1: Elucidate the mechanisms of success or failure of chhaupadi interventions to date. Via review of scientific and gray literature and key-informant interviews (n=35), we will conduct an RS [45] of extant studies/interventions to identify opportunities and develop a theoretical model to inform chhaupadi intervention design.Aim 2: Co-design a chhaupadi intervention with community members. Based on aim 1 findings, we will conduct a 2-week co-design workshop with women and girls who practice chhaupadi (n=10), guided by principles of IM, and using HCD and ABR methods to ultimately develop a culturally relevant chhaupadi intervention. We will elicit feedback on the intervention via community dialogue sessions (n=2, 10 people each), community-level key informant interviews (KIIs) (n=8), and menstrual health expert interviews at the national level (n=8). Additional insights will be gathered via rapid situation analysis in 4 additional chhaupadi practicing communities to understand how the intervention may need to be tailored to specific contexts in future scale-up work (n=75 interviews).Aim 3: Pilot the chhaupadi intervention with community members to assess feasibility and acceptability. Two matched communities will be identified and randomly assigned to intervention and control (menstrual education only) at the community level (n=25 intervention, n=25 control). Surveys and focus groups with participants will be conducted to assess feasibility, acceptability, and changes in health attitudes and behaviors.

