Eligibility criteria for the clinical trial will be refined based on the target groups of the final intervention developed in aim 2, but are expected to include women and girls who currently practice chhaupadi and have been residents of the communities for at least one year. We will use a sample size that allows for preliminary testing of feasibility and acceptability. Before enrolling, the research team will screen participants based on eligibility criteria, obtain informed consent, and document reasons for nonparticipation, if necessary. Communities will be randomized into the intervention or control group to eliminate bias; the control group will receive health education materials only.

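### The pilot's feasibility results are set against fixed benchmarks with no measure of precision planned, and Table 3 does not say whether retention is judged per community or pooled

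*Protocol article*

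**What the plan says.** The Specific Aims section fixes the size of the Aim 3 pilot at "n=25 intervention, n=25 control", with one community per arm. The only rationale for that size is in Study Population and Recruitment: "We will use a sample size that allows for preliminary testing of feasibility and acceptability". No precision figure is attached to it.

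Table 3 gives the thresholds. For enrolment and retention the entry reads "Benchmark: ≥80% of approached individuals enrolled; ≥80% retention". For the feasibility scale it reads "a valid and reliable measure of feasibility with 4 items on a 5-point Likert scale (Benchmark: ≥3.5", and the same 3.5 is set for acceptability and appropriateness.

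Specific Analysis Plans for Aim 3 says how they are used: enrolment and completion rates are to be "compared with prespecified benchmarks (Table 3". The same sentence then lists what will be reported: "outcomes for each measure (frequency and %, mean and SD, or median and range". The section states that the pilot is not powered for between-arm comparisons. It does not mention the precision of the feasibility estimates. The Aim 3: Pilot Trial section says that the results will feed into the design of a later trial.

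**The concern.** Feasibility and acceptability are the stated purpose of the pilot, so the rates and scores set against Table 3 are its main results. The one caveat about size concerns comparisons between arms. The quantities actually compared with a benchmark are single rates and single scores, and the caveat does not cover them. An SD describes the spread between participants and is not the precision of a mean. A bare percentage from 25 people looks firmer than it is.

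The retention denominator matters as well. The intervention is estimated at 8 to 10 two-hour sessions over 4 months, while the control community receives health education materials only, so retention could well differ between the two. A single pooled rate could look acceptable while the rate that matters for the intervention does not.

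At stake is the planning of the next trial. If it is sized for 80% retention when the pilot data leave much lower values open, it may recruit too few participants.

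**Working it through.** **No figure to reproduce.** The article gives no power or precision calculation for 25 per arm. What follows is the precision implied by its own sample size and thresholds.

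**Inputs.** From the article: n = 25 per community and 50 in total (Specific Aims); 80% enrolled, 80% retained and scores of 3.5 (Table 3). Assumed: two-sided 95% intervals; independent participants; the 3.5 benchmark applied to the mean score across respondents; a score SD of 0.5 to 1.0, since no SD is given; and completion in the text taken to mean retention in Table 3.

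**Proportions.** The exact (Clopper-Pearson) limits for x out of n are the 2.5% quantile of Beta(x, n − x + 1) and the 97.5% quantile of Beta(x + 1, n − x).

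| Result | Observed | Exact 95% CI | Wilson 95% CI |
|---|---|---|---|
| Retention, one community, 20/25 | 80% | 59.3% to 93.2% | 60.9% to 91.1% |
| Retention, pooled, 40/50 | 80% | 66.3% to 90.0% | 67.0% to 88.8% |
| Enrolment, 50 of 62 approached | 80.6% | 68.6% to 89.6% | 69.1% to 88.6% |

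The enrolment denominator is people approached, not people enrolled. To enrol 50 at 80%, 50/0.80 = 62.5 people are approached, so about 62.

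**How high the result must be before the interval excludes values below 80%.** In one community, 24/25 has an exact lower limit of 79.6%, so 25/25 is needed (86.3%). Pooled, 45/50 gives 78.2% and 46/50 gives 80.8%, so 46/50 is needed.

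**Chance that the observed rate reaches 80%.** This is P(X ≥ 20) for n = 25 and P(X ≥ 40) for n = 50, with X binomial.

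| True retention | n = 25 | n = 50 |
|---|---|---|
| 70% | 19% | 8% |
| 75% | 38% | 26% |
| 80% | 62% | 58% |
| 85% | 84% | 88% |

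These figures show how weakly an observed rate near 80% separates adequate from inadequate retention at this size.

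**Pooling.** If 17/25 (68%) are retained in the intervention community and 23/25 (92%) in the control community, the total is (17 + 23)/50 = 40/50 = 80%. The pooled rate sits on the benchmark while the intervention community is 12 points below it.

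**Mean scores.** The 95% half-width is t(0.975; 24) × SD/√25 = 2.064 × SD/5. That gives ±0.21 for an SD of 0.5, ±0.31 for 0.75 and ±0.41 for 1.0.

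**The case against.** The strongest reply is that a journal article condenses its protocol. Interval methods and per-arm displays are ordinary content for an analysis plan, which may exist but is not shown, and nothing in the article is false or contradictory. The list of summaries does not say that intervals are excluded, and a reader could derive them from n and percentage or from mean and SD. This lowers the weight of the point but does not remove it. The article does not leave the matter open: it states the comparison, the thresholds and the summaries to be reported, and precision is not among them.

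A reader might infer that the plan declares a benchmark met or missed and moves to a trial on that basis. The article does not support this. It states no progression rule, says only that the results inform a later trial, and sets focus groups, open-ended questions and session completion beside the benchmarks. The probabilities of reaching 80% therefore illustrate sampling noise and are not error rates of a rule in the plan. Adding intervals would not change them either; it would change how the result is read.

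A reader might also apply 25 to every benchmark. That fits retention in one community and participants' scores in the intervention community. Enrolment has about 62 in the denominator, and acceptability is also rated by implementers, whose number is not given.

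Finally, it would be too strong to say that the plan pools. The three scale benchmarks are ratings of the intervention, so pooling them with the control community is unlikely. Pooling is only a possible reading for enrolment and retention, because Table 3 does not say.

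**Conclusion.** The point holds as a matter of precision and interpretation. As written, the main feasibility results would be set against thresholds with no measure of uncertainty, and the retention benchmark has no stated denominator. Exact intervals at the benchmark run about 34 percentage points for one community (59% to 93%), 24 pooled (66% to 90%) and 21 for enrolment (69% to 90%). The proportions rest on independent participants. With one community per arm, carrying the result to other communities is less certain still. The half-widths for scores also rest on assumed SDs. This is not an arithmetic error, nor a fault in a decision rule, since the article contains no such rule. It is a low-cost improvement that affects what the pilot can say for the next trial, and Aim 3 data collection has not begun.

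**What to change.** In Specific Analysis Plans for Aim 3, state that each benchmarked result will be reported with a 95% CI: exact or Wilson for proportions, t-based for mean scores. In Table 3, state that enrolment and retention are shown by community and that the retention benchmark is judged in the intervention community. Add that the interval as well as the point estimate will be used when planning attrition and recruitment for the later trial.

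The cost is one or two sentences of text and a few lines of Stata code. Design, sample size and conduct are unchanged. The wording of the results will be somewhat less favourable.

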For aim 2, we will establish one CDT of 10 participants to work with the study team to co-design a chhaupadi intervention. Sample size is guided by standards in the literature for the ideal focus group size. The CDT will be comprised of women and girls who practice chhaupadi (menstruating age and older), from diverse backgrounds including occupation, age, caste/ethnicity, religion, literacy, and marital status. CDT participants will be recruited via snowball sampling and through community-level collaborators who have strong ties with local NGOs and government leaders. The CDT and all participants will be compensated for their time. Community dialogue sessions (2, n=10) will include youth, elders, religious leaders, teachers, health care workers, and other community members who can speak to the potential for a chhaupadi intervention in the community. We will also conduct KIIs (n=8) with key community leaders such as local police, government leaders, and activists with chhaupadi expertise to inform our overall understanding of the context.

The “rapid situation analysis,” will focus on gathering quick snapshots from a variety of chhaupadi-practicing districts, from a range of community members, including key informants (eg, police, teachers, health post in charge, members of government), to those with lived experience practicing chhaupadi. The participants will be selected in partnership with the local municipality office of each study district.

Finally, the “insight workshop,” which will be held at the district level in one of the chhaupadi-practicing districts to ensure accessibility for community members and local leaders, will bring together the original CDT members from aim 2.

In aim 3, two communities (1 intervention and 1 control) will be selected in one chhaupadi-practicing district of Nepal with high prevalence of chhaupadi based on the latest evidence at the time of data collection. We seek to identify communities that have not been exposed to a chhaupadi intervention in the past 5 years. Control and intervention communities will be matched based on exposure to chhaupadi interventions, population, rurality, and caste/ethnic makeup.

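### Letting baseline significance tests choose the covariates, with 25 per arm, will often leave small-to-moderate imbalance unadjusted and does not secure use of the Pre outcome values

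*Protocol article*

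**What the plan says.** The rule is in the protocol article under Specific Analysis Plans for Aim 3: "We will also test for differences in potential confounders between the intervention and control groups and adjust for them in regression models". It names no covariates and gives no significance level.

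The same paragraph limits the purpose of the comparison: "This pilot is not intended to power between-arm comparisons", and "no formal efficacy tests will be conducted by the comparison group". It does not say what the adjusted regressions are for.

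The setting is as follows.

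- **Size and allocation.** Specific Aims has two matched communities allocated "at the community level (n=25 intervention, n=25 control". Study Population and Recruitment confirms "two communities (1 intervention and 1 control) will be selected in one chhaupadi-practicing district of Nepal".
- **Matching.** "Control and intervention communities will be matched based on exposure to chhaupadi interventions, population, rurality, and caste/ethnic makeup". All four factors describe communities, not individual participants.
- **Baseline data.** Table 3 collects six example characteristics at Pre: "Demographics (eg, sex, caste/ethnicity, religion, education, occupation, and age". It also ticks Pre, Post and 6 month for all four exploratory outcomes: anxiety, reproductive health, self-efficacy, and "Chhaupadi knowledge, attitudes, and behaviors".

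**The concern.** A covariate distorts an arm comparison when it differs between arms and also predicts the outcome. A baseline p-value speaks only to the first condition, and with 25 per arm it does so weakly. A covariate that predicts the outcome strongly but differs moderately between arms is likely to be left out. One that predicts nothing may be let in by chance. The covariate set is then known only after the data are seen.

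This matters more here than in an individually randomised trial. Only two communities are allocated, so nothing balances participants between arms on age, education or baseline outcome level. Real differences are plausible.

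At stake are the adjusted summaries of the exploratory outcomes. The Aim 3: Pilot Trial section says the results should inform the design of a later trial. The Pre value of each outcome is likely to be among its best predictors and is already collected, but nothing in the rule guarantees its use.

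**Working it through.** The article gives no power, effect size or significance level for Aim 3, so there is no stated figure to reproduce.

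**Inputs.** 25 per arm and one community per arm (Specific Aims; Study Population and Recruitment). Six candidate characteristics (Table 3). Assumed, because not stated: two-sided 5% tests; imbalance d of 0.2 to 1.0 SD; covariate-outcome correlation r of 0.5 or 0.7; intracluster correlation of 0.01 to 0.10.

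**1. When a continuous covariate is selected.** The two-sample t-test has 48 degrees of freedom and a critical value of 2.011. The standard error of the difference is √(2/25) = 0.283 SD. The observed difference must exceed 2.011 × 0.283 = 0.57 SD.

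**2. Power.** The noncentrality parameter is d × √(25/2). For d = 0.5 it is 0.5 × 3.536 = 1.77.

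| True imbalance (SD) | Detected | Missed |
|---|---|---|
| 0.2 | 11% | 89% |
| 0.3 | 18% | 82% |
| 0.5 | 41% | 59% |
| 0.6 | 55% | 45% |
| 0.8 | 79% | 21% |
| 1.0 | 93% | 7% |

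Even odds fall at d = 0.57, and 80% power at d = 0.81. For a binary covariate, 50% against 70% is detected 30% of the time (normal approximation) or 23% (Fisher); 50% against 80%, 61% or 51%.

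**3. Spurious selection.** With six independent tests and no true imbalance, the chance of at least one selection is 1 − 0.95⁶ = 26%. If sex does not vary, because women and girls are the expected participants, five tests give 1 − 0.95⁵ = 23%. Correlation among the covariates would change these figures.

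**4. Effect on the estimate.** Simulation with 20,000 replicates per setting, 25 per arm and a true effect of zero. Covariate X has SD 1 and is shifted by d in one arm; outcome Y = rX + √(1 − r²) × noise. Entries are bias in outcome SD. As a check, unadjusted bias should be about r × d, for example 0.5 × 0.5 = 0.25.

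| r | d | No adjustment | Adjust only if p < 0.05 | Always adjust |
|---|---|---|---|---|
| 0.5 | 0.3 | 0.15 | 0.09 | 0.00 |
| 0.5 | 0.5 | 0.25 | 0.09 | 0.00 |
| 0.5 | 0.8 | 0.40 | 0.04 | 0.00 |
| 0.7 | 0.3 | 0.21 | 0.13 | 0.00 |
| 0.7 | 0.5 | 0.35 | 0.13 | 0.00 |
| 0.7 | 0.8 | 0.56 | 0.06 | 0.00 |

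The type I error of the test-first rule stayed between 3.7% and 6.5%, so the cost is mainly residual bias and lost precision. With no true imbalance, always adjusting lowers the SD of the estimate from 0.275 to 0.248 (r = 0.5) or from 0.265 to 0.204 (r = 0.7) compared with the test-first rule.

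**5. What adjustment cannot do.** With one community per arm, community variation alone gives the arm difference an SD of √(2 × ICC): √0.02 = 0.14 at an ICC of 0.01, and √0.20 = 0.45 at 0.10. The simulation contains no such term.

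**The case against.** **The rule may be milder than it looks.** The pronoun in the sentence could refer to all potential confounders, with the tests being descriptive only. That reading is possible but leaves the tests without a function. Test-based selection remains the natural reading, and the wording should be settled either way.

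**A reader might infer that the plan ignores baseline outcome scores.** The text does not support this. It lists no confounders and excludes none, and a covariate list may sit in an analysis plan that is not shown. What stands is narrower: the stated rule does not secure their use.

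**A reader might infer that the tests usually miss any real confounding.** That holds only below about 0.57 SD. At 0.8 SD the test finds about four in five imbalances, and the residual bias falls to 0.04 to 0.06 SD.

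**A reader might turn the precision gain into extra participants.** At an assumed pre-post correlation of 0.5, residual variance falls by 25%, and 25/0.75 suggests 33 per arm. That conversion treats participants as independently allocated. With one community per arm they are not, so the equivalence does not apply.

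**The consequence is limited.** No formal efficacy tests are planned, the outcome measures are labelled exploratory, and the pilot's main purpose is feasibility and acceptability. All of this stands. Matching may also reduce community-level differences, though it does not ensure balance between the individuals enrolled.

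**Conclusion.** The point holds in limited form. Read naturally, the plan lets baseline significance tests choose the covariates. At 25 per arm that rule passes over imbalances below about 0.57 SD more often than it finds them, and in the simulated settings at 0.3 and 0.5 SD it leaves a bias of 0.09 to 0.13 SD that fixed adjustment for the same covariate removes. These sizes rest on an assumed two-sided 5% level and assumed correlations of 0.5 and 0.7.

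Neither approach overcomes the complete overlap of arm and community. Enrollment, retention, acceptability, appropriateness and feasibility are judged against fixed benchmarks and are untouched. This is a modest correction to the exploratory analysis. It is worth making because the better method needs only data already planned and would also settle how the adjusted regressions fit with the absence of formal efficacy tests.

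**What to change.** In Specific Analysis Plans for Aim 3:

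- Delete the baseline significance tests and describe baseline characteristics by arm without p-values.
- For any adjusted between-group summary that is kept, use the same prespecified covariates in every model: the Pre value of the outcome being modelled plus a short named set, for example age and education. With 50 participants the set should stay small.
- Label these summaries descriptive, consistent with the decision not to run formal efficacy tests by comparison group.
- State that, with one community per arm, covariate adjustment cannot separate the intervention effect from differences between the communities.

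The cost is a few sentences. No new data are needed, and Aim 3 data collection is not projected to begin until Winter 2027, so the covariates can be fixed before any outcome is seen.
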